### Liquid chromatography–mass spectrometry (LC–MS) for metabonomic analysis

An ACQUITY UPLC I-Class system (Waters Corporation, Milford, USA) coupled with a VION IMS QTOF mass spectrometer (Waters Corporation, Milford, USA) will be used to analyze the metabolic profile in both ESI positive and ESI negative ion modes.

### Proposed outcome measurement

#### Primary outcome

The clinical pregnancy rate will be the primary outcome. The clinical pregnancy rate is defined as the ratio of the clinical pregnancy (one or more observed gestational sacs with a fetal heartbeat in the uterus under ultrasonography 28 days after embryo transfer) to the number of transplant cycles.

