### Intervention

For the intervention group, a live *Lactobacillus* capsule (> 1 × 10^6^ CFU/g, National Medicine Approval Number: S20030005, Inner Mongolia Shuangqi Pharmaceutical Co., Ltd., PRC) will be administered vaginally.

The live *Lactobacillus* capsule has been reported to be effective for bacterial vaginosis treatment with fewer adverse effects than antibiotics, and probiotic treatment for women with GDM has been reported to improve maternal and infant health outcomes [10, 17–19]. In the intervention group, 1 live *Lactobacillus* capsule per day will be applied transvaginally for 10 consecutive days starting on the initiation day of the FET cycle. Medical gloves will be included in the pill box, and the pills will be stored at 2–8 °C until use. The usage will be explained to the participants by the CRCs. A well-designed medication diary will be prepared to help remind patients and assist them in recording the process of medication administration (Table 2). Regular follow-up will be performed on day 5 and day 10 in both groups by phone call. Any adverse response will be recorded and reported at any time.

**Table 2 Tab2:** Medication diary

Medication diary			
Name:			
Date	Day Month Year	Day Month Year	Day Month Year
Live *Lactobacillus* capsule for vaginal use	□ Morning □ Evening ______pill	□ Morning □ Evening ______pill	□ Morning □ Evening ______pill
	Day Month Year	Day Month Year	Day Month Year
	□ Morning □ Evening ______pill	□ Morning □ Evening ______pill	□ Morning □ Evening ______pill
	Day Month Year	Day Month Year	Day Month Year
	□ Morning □ Evening ______pill	□ Morning □ Evening ______pill	□ Morning □ Evening ______pill
	Day Month Year		
	□ Morning □ Evening ______pill		

Please fill out the date and time after the daily use of 1 capsule

Please contact us if any symptoms of discomfort occur during medication use

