### Participant timeline

The time schedule of enrollment, intervention, follow-up and outcome assessments is shown in Table 3. After undergoing ovulation, egg retrieval, IVF, and advanced embryo freezing, PCOS patients will move on to the next step of endometrial preparation for FET. The duration of endometrial preparation will continue for approximately 14 days. At the 1st clinical visit on the first day of the current FET cycle, written informed consent, baseline information, 2 vaginal swabs, 2 cervical canal swabs, and 3 ml peripheral blood will be obtained at enrollment. After quick screening for the relative abundance of *Lactobacillus* spp. in vaginal flora, the participants will be informed of whether they have LGT dysbiosis and the results of randomization. At the 2nd visit after enrollment, in the control group, participants with LGT dysbiosis will confirm the next contact, while the intervention group will administer live *Lactobacillus* capsules vaginally and will be provided a medication diary. All participants will be followed up 5 times in the clinic or by phone call. The 3rd visit after 5 days of drug administration will mainly be about whether any adverse response occurs. At the 4th visit after 10 days of drug administration, the medication diary will be checked and reviewed, and any adverse response will be recorded and reported. At the 5th visit on the day of ET, 2 vaginal swabs, 2 cervical canal swabs, and 3 ml peripheral blood will be obtained from participants in both groups. At the 1st follow-up after 14 days of ET, human chorionic gonadotropin (HCG) and progesterone (P) levels will be determined as standard clinical procedures. If the HCG test is positive, the 2nd follow-up will occur approximately 5 weeks after ET, and clinical pregnancy will be confirmed by ultrasound and recorded in the CRIP system. At the 3rd follow-up, the fetal developmental situation and maternal obstetric complications at approximately 24-28 gestational weeks, if any, will be carefully recorded. The endpoint of follow-up is live birth, and maternal and neonatal information will be obtained.

**Table 3 Tab3:** Schedule

	1st visit on FET initial day	2nd visit after enrollment	3rd visit after 5 days	4th visit after 10 days	5th visit on ET	1st follow-up at 14 days after ET	2nd follow-up at 5 weeks after ET	3rd follow-up at mid-pregnancy	End of live birth

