#### Secondary outcomes

##### Maternal outcomes

The implantation rate is defined as the number of gestational sacs in the uterus divided by the number of embryos transferred. The live birth rate is defined as the delivery of any viable infant at 25 weeks of gestation or more after initial embryo transfer to the number of transplant cycles. The biochemical pregnancy rate is defined as the ratio of biochemical pregnancies (serum hCG level >5 mIU/L 14 days after embryo transfer) to the number of transplant cycles. The spontaneous abortion rate is defined as the ratio of spontaneous abortions (spontaneous pregnancy loss before 20 weeks of gestation) to the number of transplant cycles. The ongoing pregnancy rate is defined as the ratio of ongoing pregnancies (intrauterine live fetus under ultrasonography after 20 weeks of gestation) to the number of transplant cycles. The preterm birth rate is defined as the ratio of preterm births (delivery at ≥ 28 and < 37 weeks of gestation) to the number of transplant cycles. Pregnancy complications, including GDM, hypertensive disorders of pregnancy, including gestational hypertension and preeclampsia, placental abruption, preterm/prelabor/rupture of membranes, birth mode (vaginal delivery/operational vaginal delivery/selective or emergency cesarean section), blood loss during birth, and postpartum hemorrhage, adherence to the intervention and maternal mortality, will be followed up and assessed. A GDM diagnosis will be made according to the diagnostic criteria of the American Diabetes Association based on the results of the 75-g oral glucose tolerance test (OGTT) at 24–28 gestational weeks (fasting venous glucose level ≥ 5.1 mmol/L, 1-h value ≥ 10.0 mmol/L, 2-h value ≥ 8.5 mmol/L) [21]. Gestational hypertension is defined as de novo hypertension (≥ 140/90 mmHg) after 20 gestational weeks without proteinuria. Preeclampsia will be diagnosed when gestational hypertension is comorbid with any of the following manifestations: proteinuria (≥ 0.3 g/24 h), renal insufficiency, thrombocytopenia (platelets ≤ 100,000 × 10^9^/L), impaired liver function or pulmonary edema [22].

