#### Statistical analysis

Categorical variables will be presented as counts with percentages, e.g., *n* (%). Normally distributed data will be shown as the means with standard deviations, e.g., means ± SDs, while nonnormally distributed data will be expressed as medians with interquartile ranges, e.g., medians (IQRs). Student’s *t* test for continuous variables with normal distributions and the nonparametric

Kruskal–Wallis test for nonnormally distributed data will be applied for comparisons of significant differences between the 2 groups. The Pearson chi-square test will be used for categorical data. For binary observational endpoints, risk ratios with 95% confidence intervals will be calculated by binomial regression with and without adjustment for potentially confounding baseline values. In this study, the main analyses will be conducted using an intention-to-treat (ITT) model, in which all participants will be included based on random assignment regardless of study completion. For outcomes collected at different time points, a repeated measurements design using a generalized estimating equation (GEE) model will be used to fit outcomes that are measured at each time point so that all the participants might be included in the analyses, even if there are missing data for some of the follow-up points. A multiple imputation model will be used to process the missing data. Additionally, statistical analyses of the baseline characteristics of participants who remain in the study and those who are lost to follow-up will also be performed to explore whether there is differential dropout. All statistical analyses will be conducted using the SPSS software (version 25.0) and R software (version 4.0.2). A two-sided *p* value < 0.05 will be considered significant.

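### The primary pregnancy rate is divided by transplant cycles while the main analysis is declared ITT, and nothing says how a randomised woman without a transfer is counted

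*Protocol article*

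**What the plan says.** The Primary outcome section defines the clinical pregnancy rate as pregnancies with a gestational sac and fetal heartbeat "in the uterus under ultrasonography 28 days after embryo transfer) to the number of transplant cycles". Under Maternal outcomes and Neonatal outcomes, the rates of live birth, biochemical pregnancy, spontaneous abortion, ongoing pregnancy, preterm birth and birth defects use the same denominator. The implantation rate is per embryo transferred.

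The Statistical analysis section declares an intention-to-treat main analysis in which "all participants will be included based on random assignment regardless of study completion". It adds: "A multiple imputation model will be used to process the missing data".

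The order of events is in Participant timeline, Table 3 and Intervention. Consent is on the first day of the FET cycle. After the quick screen, "the participants will be informed of whether they have LGT dysbiosis and the results of randomization"; Table 3 puts allocation at the 2nd visit. The capsule is used "for 10 consecutive days starting on the initiation day of the FET cycle". On preparation before transfer: "The duration of endometrial preparation will continue for approximately 14 days". Transfer itself is at the 5th visit. Recruitment and randomization states that investigators and participants know the arm.

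**The concern.** The two rules describe different sets of women. Someone who is randomised and then has no transfer, whether through withdrawal, postponement or a clinical decision, belongs to the ITT set but adds no completed transfer to the denominator. Reaching transfer is an event after randomisation and after treatment, so a per-transfer comparison conditions on something that the allocated arm, or knowledge of it, could influence. If poor-prognosis cycles were stopped more often in one arm, that arm's per-transfer rate would rise with no effect of the capsule.

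There is also a plainer problem. Two analysts who both follow the article could use different denominators for the primary endpoint and report different results.

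**Working it through.** **Inputs from the protocol article**
- Planning control rate 17.65%; a 20% increase read as absolute, giving 37.65%; one-sided alpha 0.025; power 95%; dropout 15%; 130 per group calculated, 150 per group to be recruited (Sample size calculation).
- A further base rate of 26%, the meta-analysis figure in the same section.

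**Assumed, because not given:** cancellation of 5% in control, and 5%, 10% or 15% in intervention.

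**Step 1. The plan's own figure.** Pooled two-proportion formula, mean rate (0.1765 + 0.3765)/2 = 0.2765:

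n = [1.960·√(2·0.2765·0.7235) + 1.645·√(0.1765·0.8235 + 0.3765·0.6235)]² / 0.20² = (1.240 + 1.014)² / 0.04 ≈ 127 per arm, or 254 in total.

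This is close to the stated 260, and 254/0.85 ≈ 299 matches the target of 300. The sample size is not in error on this point.

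**Step 2. What the denominator does under no effect.** Let p be the rate in either arm if every woman had her transfer, c the fraction cancelled in an arm, and s the prognosis of cancelled women relative to the average (0 = all would have failed, 1 = unrelated to prognosis). Then:
- per transfer: p(1 − s·c)/(1 − c)
- per woman randomised, no transfer counted as no pregnancy: p(1 − s·c)

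With s = 1 the per-transfer rate is p whatever c is, so there is no bias. With c and s the same in both arms there is no bias either. With s = 0, for example p = 17.65% and c = 5% vs 15%: 17.65/0.95 = 18.6% vs 17.65/0.85 = 20.8%, a spurious +2.2 points.

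**Step 3. Type I error of the per-transfer test.** Simulation of a pooled z-test, two-sided 5%, 150 randomised per arm, 400,000 runs (the last digit can move by about 0.1):

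| Base rate p | Cancelled, control vs intervention | Per-transfer rates, s = 0 | Spurious difference, s = 0 | Type I error, s = 0 | Difference and error, s = 0.5 |
|---|---|---|---|---|---|
| 17.65% | 5% vs 10% | 18.6% vs 19.6% | +1.0 | 5.5% | +0.5; 5.1% |
| 17.65% | 5% vs 15% | 18.6% vs 20.8% | +2.2 | 7.4% | +1.1; 5.7% |
| 26% | 5% vs 10% | 27.4% vs 28.9% | +1.5 | 6.0% | +0.8; 5.3% |
| 26% | 5% vs 15% | 27.4% vs 30.6% | +3.2 | 9.1% | +1.6; 6.1% |
| 37.65% | 5% vs 10% | 39.6% vs 41.8% | +2.2 | 6.6% | +1.1; 5.5% |
| 37.65% | 5% vs 15% | 39.6% vs 44.3% | +4.7 | 12% | +2.3; 6.9% |

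With 5% cancelled in both arms the error is 5% at every base rate. In the s = 0 rows the per-randomised test also stays at 5%.

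**Step 4. Power if the rate is defined per woman randomised.** Multiply 17.65% and 37.65% by (1 − c), with equal c and 150 per arm:
- c = 0: 17.65% vs 37.65%, power 97.5%
- c = 5%: 16.8% vs 35.8%, 96.6%
- c = 10%: 15.9% vs 33.9%, 95.4%
- c = 15%: 15.0% vs 32.0%, 93.9%

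The risk ratio is 2.13 throughout. The absolute difference goes from 20 to 19, 18 and 17 points.

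**The case against.** **The term is undefined.** The article dates the start of the FET cycle to enrolment. If a transplant cycle means an FET cycle started, the denominator is close to the number randomised and agrees with the ITT statement. That reading is possible, but the definition times the outcome from the transfer, so completed transfers is the more natural one. The ambiguity is itself a reason to fix the wording.

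**Bias needs two conditions.** Cancellation must differ between arms and be related to prognosis. The article gives no cancellation rate and no reason to expect a difference, and its Discussion already concedes that lack of blinding may introduce bias. This stands: the s = 0 columns are an extreme, and bias is possible rather than shown.

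**Three stronger readings are tempting and not supported.**
- A reader might infer that women with repeat transfers are counted twice. The schedule describes one current FET cycle and one transfer visit ("At the 5th visit on the day of ET"), with follow-up counted from it.
- A reader might infer that live birth mixes a numerator from the first transfer with a denominator of all cycles, since it is defined as "delivery of any viable infant at 25 weeks of gestation or more after initial embryo transfer to the number of transplant cycles". With one transfer per woman the two agree.
- A reader might infer that pregnancies will be imputed for women who received no embryo. The article does not class a cancelled transfer as missing data, so this would follow only if an analyst treated it so.

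**The alternative is not neutral either.** If one arm cancels more for reasons unrelated to prognosis, the per-randomised rates differ: at 17.65% with 5% vs 15% cancelled, 16.8% vs 15.0%. That is a real consequence of allocation and part of an ITT effect, but it is a reason to show both rates.

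**Conclusion.** The conflict is real. The stated primary denominator, read naturally, leaves out randomised women without a transfer; the stated analysis set keeps them; and no section reconciles the two. This goes beyond detail that an analysis plan could supply, because the article fixes both rules itself.

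The size cannot be derived from the article. Under no true effect, the spurious difference runs from 0 points (type I error 5%), through +1.0 to +2.2 points (about 5.5–6.6%) at 5% vs 10% cancelled, to +2.2 to +4.7 points (about 7.4–12%) at 5% vs 15%. The non-zero figures assume that every cancelled woman would have failed. At the plan's own control rate of 17.65% they are the smallest in each range, and at half the average prognosis they shrink to at most +2.3 points and 6.9%.

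This should be fixed before analysis. It does not invalidate the design or the sample size.

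**What to change.** In the outcome definitions:
- Define clinical pregnancy, and likewise biochemical pregnancy, ongoing pregnancy and live birth, per woman randomised for the index FET cycle.
- Count a known absence of transfer as no pregnancy in that cycle.
- Use multiple imputation only where the outcome is truly unknown.
- Report per-transfer rates as supportive, with the number of and reasons for non-transfer by arm.

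The cost is wording. Treatment and schedule do not change. Reported rates will be slightly lower than per-transfer rates, and power at 150 per arm falls from 97.5% to about 94–97% with 5–15% cancelled equally, before any other loss to follow-up. Under this definition, 95% power would need 274, 294 or 318 women in total at 5%, 10% or 15% cancelled, so the planned 300 is enough up to about 10%.

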#### Secondary outcomes

##### Maternal outcomes

The implantation rate is defined as the number of gestational sacs in the uterus divided by the number of embryos transferred. The live birth rate is defined as the delivery of any viable infant at 25 weeks of gestation or more after initial embryo transfer to the number of transplant cycles. The biochemical pregnancy rate is defined as the ratio of biochemical pregnancies (serum hCG level >5 mIU/L 14 days after embryo transfer) to the number of transplant cycles. The spontaneous abortion rate is defined as the ratio of spontaneous abortions (spontaneous pregnancy loss before 20 weeks of gestation) to the number of transplant cycles. The ongoing pregnancy rate is defined as the ratio of ongoing pregnancies (intrauterine live fetus under ultrasonography after 20 weeks of gestation) to the number of transplant cycles. The preterm birth rate is defined as the ratio of preterm births (delivery at ≥ 28 and < 37 weeks of gestation) to the number of transplant cycles. Pregnancy complications, including GDM, hypertensive disorders of pregnancy, including gestational hypertension and preeclampsia, placental abruption, preterm/prelabor/rupture of membranes, birth mode (vaginal delivery/operational vaginal delivery/selective or emergency cesarean section), blood loss during birth, and postpartum hemorrhage, adherence to the intervention and maternal mortality, will be followed up and assessed. A GDM diagnosis will be made according to the diagnostic criteria of the American Diabetes Association based on the results of the 75-g oral glucose tolerance test (OGTT) at 24–28 gestational weeks (fasting venous glucose level ≥ 5.1 mmol/L, 1-h value ≥ 10.0 mmol/L, 2-h value ≥ 8.5 mmol/L) [21]. Gestational hypertension is defined as de novo hypertension (≥ 140/90 mmHg) after 20 gestational weeks without proteinuria. Preeclampsia will be diagnosed when gestational hypertension is comorbid with any of the following manifestations: proteinuria (≥ 0.3 g/24 h), renal insufficiency, thrombocytopenia (platelets ≤ 100,000 × 10^9^/L), impaired liver function or pulmonary edema [22].

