**Methods/design:**

This is a protocol for a multicenter, open-label, randomized controlled trial in China. Women diagnosed with PCOS who are undergoing IVF-FET treatment will be recruited. Allocation to the intervention/control arms at a ratio of 1:1 will be executed by an electronic randomization system. Participants in the intervention arm will receive the live *Lactobacillus* capsule vaginally for 10 consecutive days before embryo transfer, while those in the control arm will receive standard individualized care. The primary outcomes will be the clinical pregnancy rate, implantation rate, and live birth rate. 16S rRNA sequencing and liquid chromatography–mass spectrometry will be conducted to evaluate the LGT microbiome and systemic metabonomics before and after the intervention. A sample of 260 participants will provide 95% power to detect a 20% increase in the rate of clinical pregnancy (*α* = 0.025, one-tailed test, 15% dropout rate). A total of 300 participants will be recruited.

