### Recruitment and randomization

The clinical research coordinators (CRCs) will verbally inform PCOS patients that the hospital is currently conducting a multicenter clinical trial to better improve the outcomes of IVF–FET in PCOS patients with vaginal microbiota dysbiosis. If they fully understand and are willing to take part in the study, they will meet a CRC in person at the hospital, sign an informed consent form, and officially join the study on the first day of the current IVF–FET cycle. The CRCs will later inform patients of whether they have vaginal microbiota dysbiosis. Basic information, including sociodemographic characteristics and clinical history, will be collected by the CRCs using standardized questionnaires and recorded into an online and password-protected electronic data collection system (Clinical Research Integrated Platform [CRIP], https://crip-ec.shdc.org.cn, supported by Shanghai Hospital Development Center, Shanghai, China), which will automatically generate a sequential code and randomly allocate participants to the intervention group or the control group at a ratio of 1:1 based on the whole study population. The research doctors will manage the study group allocation. Given the nature of vaginal use of live *Lactobacillus* capsules before FET, the investigators and participants will be informed of the assignment. To ensure the reality of this study, independent statisticians will be recruited, and they will be blinded to the group allocation.

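### Implantation is counted per embryo while women are randomised, and the stated methods for proportions make no allowance for embryos nested in a woman; if some transfers involve several embryos, the interval may be too narrow

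*Protocol article*

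**What the plan says.** All places are in the protocol article.

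- *Maternal outcomes* (under Secondary outcomes): "The implantation rate is defined as the number of gestational sacs in the uterus divided by the number of embryos transferred". The denominator is embryos. The primary outcome, clinical pregnancy, is instead a ratio "to the number of transplant cycles", and the other pregnancy rates listed there also use cycles.
- *Recruitment and randomization*: the electronic system will "randomly allocate participants to the intervention group or the control group at a ratio of 1:1". The randomised unit is the woman.
- *Statistical analysis*, for proportions: "The Pearson chi-square test will be used for categorical data", and for binary endpoints "risk ratios with 95% confidence intervals will be calculated by binomial regression with and without adjustment for potentially confounding baseline values". The significance criterion is a two-sided p "value < 0.05 will be considered significant".
- *Statistical analysis*, the only method named for correlated data: "For outcomes collected at different time points, a repeated measurements design using a generalized estimating equation (GEE) model will be used".
- *Abstract, Methods/design*: "The primary outcomes will be the clinical pregnancy rate, implantation rate, and live birth rate". The outcome sections of the main text make clinical pregnancy the only primary outcome and list implantation as secondary.

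The article assigns no test to the implantation rate by name. It does not say how many embryos are transferred per woman, and it gives no within-woman correlation.

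**The concern.** Embryos transferred together share one woman, one endometrium and one preparation regimen, so their outcomes need not be independent. Chi-square and ordinary binomial regression on pooled embryo counts treat each embryo as a separate observation. When outcomes within a woman are positively correlated, this overstates the information in the data. The standard error is then too small, the interval too narrow, and a true null is rejected more often than 5% of the time.

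The GEE sentence does not help, because two embryos placed in the same transfer are not two time points. At stake is the reported precision of the implantation comparison. It would carry more weight if the abstract's description of implantation as primary were the one that stands.

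**Working it through.** **1. The plan's own figure.** The article gives no figure for implantation. Its only calculation is for clinical pregnancy: 260 women (130 per group), 95% power, one-tailed alpha 0.025. Take the control rate as 17.65% and read the 20% increase as percentage points, so p1 = 0.1765, p2 = 0.3765 and the mean is 0.2765. With pooled variance and no continuity correction:

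n = [1.960·√(2 × 0.2765 × 0.7235) + 1.645·√(0.1765 × 0.8235 + 0.3765 × 0.6235)]² / 0.20² = (1.240 + 1.014)² / 0.04 ≈ 127 per group, 254 in total.

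That is within 2.3% of 260, and power at 130 per group is 95.4%. The calculation is per woman, so the present point does not change it.

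**2. Inputs for implantation.**

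- From the article: the embryo as unit, the woman as randomised unit, 150 women per arm, two-sided 0.05.
- Assumed: the share s of women receiving two embryos (the rest receive one), the intraclass correlation (ICC) of embryo outcomes within a woman, and, for the simulation only, an implantation rate of 0.25.

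**3. Formulas.** With m embryos per woman, the design effect is

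DE = 1 + (Σm²/Σm − 1) × ICC, where Σm²/Σm = (1 + 3s)/(1 + s).

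For s = 0.5 this gives 2.5/1.5 = 1.667, so DE = 1 + 0.667 × ICC. For s = 1 it gives 2, so DE = 1 + ICC. The real type I error of the test that ignores clustering is 2 × [1 − Φ(1.96/√DE)], and the correct interval is wider by √DE.

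**4. Results.**

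| Two-embryo transfers | ICC | DE | √DE | Real type I error |
|---|---|---|---|---|
| none | any | 1.00 | 1.00 | 5.0% |
| half | 0.1 | 1.07 | 1.03 | 5.8% |
| half | 0.3 | 1.20 | 1.10 | 7.4% |
| half | 0.5 | 1.33 | 1.15 | 9.0% |
| all | 0 | 1.00 | 1.00 | 5.0% |
| all | 0.1 | 1.10 | 1.05 | 6.2% |
| all | 0.3 | 1.30 | 1.14 | 8.6% |
| all | 0.5 | 1.50 | 1.22 | 11.0% |
| all | −0.1 | 0.90 | 0.95 | 3.9% |

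**5. Check by simulation.** Beta-binomial data were generated under the null: 150 women per arm, rate 0.25, 10,000 runs per setting. The pooled test rejected in 7.4% (half double, ICC 0.3), 9.1% (half, 0.5), 8.5% (all, 0.3) and 10.9% (all, 0.5) of runs. A test with robust variance clustered on the woman rejected in 4.8% to 5.3% in every setting with two-embryo transfers.

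**6. Is a positive ICC plausible?** The trial's rationale is that a woman-level factor, *Lactobacillus* deficiency, lowers implantation. The sample size section gives clinical pregnancy rates of 17.65% with deficiency (below 50%) and 41.82% without. Eligibility is below 80%, so women from both sides of 50% can enter. As an illustration only, assume a 50:50 mix and let these per-cycle rates stand in for implantation. The between-woman variance is (0.2417/2)² = 0.0146, the total is 0.297 × 0.703 = 0.209, and the ICC is about 0.07. With all double transfers the type I error would be about 5.8%. This supports the sign, not any particular size.

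**The case against.** The strongest reply is that the article never says embryos will be the units of a test. Its rules are general and sorted by type of data, and the intention-to-treat sentence speaks of participants. A ratio of sacs to embryos computed for each woman could be compared with the rank test that the article names for non-normal data, and that would respect the randomised unit. A full analysis plan, not shown, may also specify clustering.

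Part of this stands. A reader might infer that the plan prescribes a chi-square test on embryo counts; it does not do so by name. That is only the natural reading of the general rules. The per-woman reading is possible but strained, because the outcome is defined as one pooled ratio of sacs to embryos. Nor is the point simply that detail was left to another document: the rules the article does state, applied to an outcome it does define, do not fit.

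A second reply is that every transfer might be of a single embryo, in which case nothing is wrong. The article does not exclude this. However, it sets no single-embryo restriction, its clinical pregnancy definition allows for more than one sac, and it uses a separate embryo denominator that would coincide with cycles if every transfer were single. Multi-embryo transfer is therefore contemplated, though not shown to occur.

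A reader might also infer that infant outcomes suffer the same error. The article states no unit or test for most of them, and the birth defect rate is per cycle, so this holds only for outcomes that are in fact analysed per infant in multiple births.

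**Conclusion.** The concern holds conditionally. The unit of the implantation rate is the embryo, the randomised unit is the woman, and no stated method for proportions allows for the nesting. If some transfers involve more than one embryo and the within-woman correlation is positive, a pooled per-embryo analysis is anti-conservative. On assumed inputs the real type I error lies between 5.0% and about 11%, with 7.4% at half double transfers and ICC 0.3, and the 95% interval is too narrow by a factor of 1 to about 1.22.

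Two stronger conclusions are not supported. The first is that the interval is certainly too narrow and the p value too small: with single-embryo transfers or an ICC of 0 there is no effect, and with a negative ICC the test is slightly conservative. The second is that the trial's main result is at risk because the abstract calls implantation primary. The outcome sections make it secondary, the trial is sized on clinical pregnancy alone, and that outcome is counted per cycle. The abstract and main text should be reconciled, but that is a separate matter.

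**What to change.** Add to *Statistical analysis* that the implantation rate is analysed with the woman as cluster, by GEE or by binomial or modified Poisson regression with robust standard errors clustered on the woman, instead of a chi-square test on pooled embryo counts. A working-independence structure keeps the estimate equal to the pooled ratio that the article defines. Apply the same rule to any neonatal outcome analysed per infant in multiple births.

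The cost is a sentence of text and slightly wider confidence intervals. GEE and R are already planned. If every transfer is of a single embryo, each cluster holds one embryo and there is no loss of precision to speak of.

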### Statistical methods

#### Sample size calculation

A recent meta-analysis reported an estimated clinical pregnancy rate of 26% in PCOS patients undergoing IVF [24]. Our team has revealed that approximately 30% of PCOS patients have *Lactobacillus* deficiency (PCOS-LD), which presents as lower levels of *Lactobacillus* (< 50%) in the vagina [7]. Our unpublished data suggested a clinical pregnancy rate of 17.65% in patients with PCOS-LD, while a clinical pregnancy rate of 41.82% was reported in PCOS patients without *Lactobacillus* deficiency (PCOS-non-LD). Moreover, our team previously reported a clinical pregnancy rate of 49.69% in patients who underwent IVF due to tubal blockage [25]. To improve the clinical pregnancy rate among infertile PCOS-LD patients to the level of that among PCOS-non-LD patients, or even to the clinical pregnancy rate among patients with tubal blockage, we hypothesized a 20% increase in the clinical pregnancy rate in our RCT. Assuming a clinically important 20% increase in the rate of clinical pregnancy in the intervention arm and allowing for a 15% dropout rate, the calculated sample size of 260 subjects (130 per group) will provide 95% power with a one-tailed alpha error of 0.025. Thus, we aim to recruit 300 women in total (150 per group).

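### The hCG cut-off for biochemical pregnancy (a secondary outcome) is printed in an implausible unit, almost certainly a slip, and should be corrected

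*Protocol article*

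**What the plan says.** The Maternal outcomes section of the protocol article builds the biochemical pregnancy rate on the count of "biochemical pregnancies (serum hCG level >5 mIU/L 14 days after embryo transfer". The rate is taken per transfer cycle. No other section gives an hCG unit or a numeric hCG threshold.

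The Participant timeline describes the day-14 visit, at which "human chorionic gonadotropin (HCG) and progesterone (P) levels will be determined as standard clinical procedures". It continues: "If the HCG test is positive, the 2nd follow-up will occur approximately 5 weeks after ET", and clinical pregnancy is then confirmed by ultrasound. The article does not name the assay, its detection limit or the laboratories' reporting unit.

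The Primary outcome section states: "The clinical pregnancy rate will be the primary outcome". That outcome is defined by ultrasound findings. Under Statistical analysis, binary endpoints are compared by risk ratios from binomial regression.

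**The concern.** The printed limit is the only numeric criterion for a named secondary outcome, and nothing else in the article lets a reader correct it. The Participant timeline treats the same day-14 test as one that sorts women into positive and negative. A limit of 0.005 mIU/mL is not a credible dividing line for that purpose.

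The outcome definition would be at stake. If the printed unit were followed, some women who are not pregnant would enter the numerator in both arms, and the comparison would be diluted. If staff ignore the printed unit, as is likely, the trial applies a cut-off that its protocol does not state. That is undesirable in an open-label trial with four centres.

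**Working it through.** The cut-off is a definition, so the plan has no calculation of its own to reproduce. The check is a unit conversion followed by an illustration.

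**1. Conversion.** Input: 5 mIU/L (Maternal outcomes).
- 5 mIU/L ÷ 1000 mL/L = 0.005 mIU/mL.
- Assumed intended limit, not in the document: 5 mIU/mL = 5000 mIU/L = 5 IU/L.
- Ratio: 5 ÷ 0.005 = 1000.

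**2. Results below the assay limit.** Let L be the lowest value that a laboratory reports. If L is above 0.005 mIU/mL, a result given only as below L could lie on either side of the printed limit and cannot be classified. The article does not give L. With L assumed to lie between 0.1 and 2 mIU/mL (100 to 2000 mIU/L), it is 100 ÷ 5 = 20 to 2000 ÷ 5 = 400 times the printed limit.

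**3. Dilution if the limit is applied literally.** Let p be the true biochemical pregnancy rate in an arm, and q the share of non-pregnant women reported above 0.005 mIU/mL, taken as equal in both arms. All truly pregnant women are assumed to exceed the limit.
- Observed rate = p + (1 − p) × q.
- Observed difference = (p₂ − p₁) × (1 − q).

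The article gives neither p nor q. With assumed true rates of 30% and 50%:

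| q | Observed rates | Difference | Risk ratio |
|---|---|---|---|
| 0 | 30% v 50% | 20 points | 50/30 = 1.67 |
| 0.5 | 65% v 75% | 10 points | 75/65 = 1.15 |
| 0.9 | 93% v 95% | 2 points | 95/93 = 1.02 |
| 1 | 100% v 100% | 0 points | 1.00 |

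The direction is fixed: for any q above 0, the difference shrinks. The amount depends wholly on q.

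**4. Is it a slip?** The same section gives a platelet criterion that begins "thrombocytopenia (platelets ≤ 100,000 × 10" and is completed as 10⁹ per litre, so a count of 100,000 is multiplied by a further 10⁹. A second implausible unit in the same section points to unchecked units rather than to a deliberate choice of limit.

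**5. Reach.** The sample size rests on clinical pregnancy rates ("Our unpublished data suggested a clinical pregnancy rate of 17.65% in patients with PCOS-LD") and a 20-point increase. For 17.65% v 37.65%, one-sided 0.025 and 95% power, the usual two-proportion formula without continuity correction gives 127 per arm, or 254 in total. The plan has 260. hCG does not enter the calculation.

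**The case against.** The strongest reply is that this is a typographical slip which nobody will follow. hCG is measured by routine clinical testing, and the visit schedule expects both positive and negative results, so the centres will in practice use their laboratories' own threshold. The primary outcome is read from ultrasound. Most of this stands, and it is why the point is minor. It does not remove the error: the article states the outcome's sole numeric criterion and states it wrongly, which differs from leaving a detail to a fuller document.

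Three stronger readings are tempting, and the document supports none of them.
- A reader might infer that essentially every woman in both arms would count as pregnant, so that the outcome carries no information. That needs literal use of the printed unit and q close to 1. The document supports neither. A result below a detection limit is indeterminate against this cut-off, or negative by ordinary laboratory convention. It is not positive.
- A reader might infer that values in the electronic data system will be converted to the printed unit. The article gives no hCG storage unit and no conversion step.
- A reader might infer that non-pregnant women would be recorded as pregnancy losses. Spontaneous abortion is defined as a loss before 20 weeks, and no rule derives it from the hCG result.

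It is also fair to object that 5 mIU/mL appears nowhere in the document. It is the natural reading of the number 5 once the unit is put right, but the sponsor has to confirm it.

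**Conclusion.** The point holds as a minor error. The conversion to 0.005 mIU/mL is certain, and the unit is almost certainly misprinted. The factor of 1000 rests on the assumption that 5 mIU/mL (5 IU/L) was intended.

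If the limit were applied as printed, non-pregnant women with measurable hCG would be misclassified, results below the assay limit could not be classified, and the contrast between arms would move towards no difference. The document does not allow that shift to be computed. The table above only shows how it varies with q under assumed true rates. The effect is confined to one secondary outcome.

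**What to change.** - Check the hCG reporting unit at the laboratories serving the four centres, then correct the unit in the Maternal outcomes definition. The intended limit is presumably >5 mIU/mL, equal to 5 IU/L, and the sponsor should confirm this.
- Reconcile the corrected definition with the positive HCG test in the Participant timeline, so that the two passages can be read together. Which rule governs follow-up is for the sponsor to decide.
- Analyse hCG in one unit across the four centres.
- Check the platelet unit in the same section at the same time.

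The cost is one corrected unit and a check of units before analysis. The design, the sample size and the primary analysis do not change.
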